### Outcomes and study measures (primary outcome, secondary outcomes)

#### Primary outcome

The primary outcome is the PCQ anxiety score at time point 2.

A comparison in anxiety score will be made between women who receive results in-person and women who receive results over the telephone.

#### Secondary outcomes

Secondary outcomes are:

PCQ anxiety score at 3-month follow-up (time point 3).PCQ anxiety score at 6-month follow-up (time point 4).Subjective understanding of results (time point 2).Measured using a survey question designed in collaboration with NHSBSP stakeholders.Objective understanding of results (time point 2).Measured using a survey question designed in collaboration with NHSBSP stakeholders.Quantitative preferences for results communication before results (time point 1).Quantitative preferences for results communication after results (time point 2).Qualitative preferences for results communication before results (time point 1).Qualitative preferences for results communication after results (time point 2).

### Analysis

#### Quantitative data—statistical analysis

A formal and more detailed statistical analysis plan will be developed by the trial team prior to the completion of recruitment.

##### Primary outcome

The primary analysis will use a mixed effects linear regression model to estimate the effects of communication method on anxiety (time point 2), after adjusting for baseline anxiety (time point 1). PCQ score will be treated as a continuous variable and to be approximately normally distributed for all analyses.

The model set-up and fixed and random effects are as follows:

Response variable—anxiety at time point 2 (PCQ).Baseline—anxiety at time point 1 (PCQ).Fixed explanatory effects (model covariates)—age, ethnicity, previous attendance, previous biopsy, education, marital status.Random effects—centre and temporal (period) effects.Comparator variable—method of communication received—telephone or in-person.

Statistical significance will be assessed at 5% level.

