### Participants and settings

This trial will be conducted in a breast screening centre setting. The study will take place in the UK where women are invited to attend breast screening every 3 years for digital mammography. The study will take place across four time points (see table 1) with a survey completed by participants at each stage. The study participants will be recruited from four English Breast Screening centres across different regions.

**Table 1 T1:** Time points for the study

Time point	Sample	Survey content	Method
Time point 1—at assessment clinic	Women attending assessment follow-up clinic	Demographic information Communication preferences Baseline anxiety score (PCQ) Contact details	In-person
Time point 2—after receiving results	Women from time point 1 who had a normal or benign biopsy	Communication preferences Repeat anxiety score (PCQ) Measure of understanding	By post
Time point 3—3-month follow-up	Women from time point 1 who had a normal or benign biopsy	Repeat anxiety score (PCQ)	By post
Time point 4—6-month follow-up	Women from time point 1 who had a normal or benign biopsy	Repeat anxiety score (PCQ)	By post

PCQ, Psychological Consequences Questionnaire.

Participants will be women between the ages of 47 and 73 attending the NHSBSP for further tests following a suspicious mammogram. This includes women offered routine screening between ages 50 and 70 and those receiving extra rounds of screening between the ages of 47 and 49 or 71 and 73 as part of the UK age extension trial.^16^ Women will be recruited at the assessment clinic pre-biopsy. However, only women who have received a benign (B2) or normal (B1) biopsy result will be included in the longitudinal data collection. Participants will not be included in the study if they presented symptomatically to the breast clinic, if they are not the recommended screening age, if they do not receive a biopsy, if they do not have English as a first or second language and if they do not have the capacity to consent.

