### Sample size considerations

In order to determine the sample size for a clustered randomised crossover study, a full specification of the important within-cluster (centre) between-period and within-period correlations is required.^23^ There is currently no available evidence on the magnitude of these correlations in our selected setting, so rather than arbitrarily selecting values we adopt a conservative approach and assume that the (within-centre) between-period correlations are zero and proceed to power as if the design were a cluster randomised design. Although the crossover aspect of the design is not explicitly accounted for in the sample size calculation, it is incorporated fully in the analysis of the primary study outcome (PCQ anxiety score at time point 2). The aim of the study is to be able to detect a clinically significant difference of 3 points in the PCQ (the difference between the score on one statement being 0, not at all, and 3, quite a lot of the time).

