**Figure 1 F1:**
[figure not shown]
Flow of required sample size for the study.

Assuming the primary outcome is approximately normally distributed, and the test is at the 5% significance level with 80% power to detect an effect of the specified size, 194 participants are required at time point 2, that is 97 participants per arm. Allowing for attrition rate between time point 1 and time point 2 due to participant withdrawal (15%) and participant eligibility (50%), a total of 457 participants will be recruited at time point 1. Participant withdrawal was calculated based on a mean response rate of 60% from previous research using postal surveys in a medical setting^24^ with a loss of 15% at each time point as a conservative estimate.

In order to account for clustering due to the recruiting centre, design effect was applied that inflated the sample size. The intra-cluster (within-centre) correlation coefficient was set to be 0.01 and the number of observations within each cluster was assumed to be equal. With the sample size of 194 women, divided by the number of centres^4^ and then divided by the number of interventions,^2^ this led to the number of observations within a cluster to be 48.2. This gave a design effect of 1.49. Taking this into account, the sample size needed to achieve statistical significance (194 women) was multiplied by the design effect, giving a total sample of 290 women at time point 2 when rounded up (see figure 1).

31 926 women are recalled for a biopsy each year. If half of the 31 926 biopsies come back as benign, this leaves a potential sample of 15 963. This means that, on average across 80 breast screening centres, each centre will have around 200 benign biopsy results each year. Therefore, assuming 50% participation rates of eligible women, recruitment will require four centres for 1 year.

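### As written, the primary model has centre and period random effects but no centre-by-period term, so any extra correlation within a centre-month makes the standard error too small; at the assumed ICC of 0.01 the effect is small

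*Protocol article*

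**What the plan says.** Under Analysis, Primary outcome, the article sets out a linear mixed model for the time point 2 PCQ score, adjusted for the time point 1 score and six covariates. Its clustering part is one line: "Random effects—centre and temporal (period) effects". Under Secondary outcomes, the 3- and 6-month scores are to be analysed in the same way.

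The section Sample size considerations says that "a full specification of the important within-cluster (centre) between-period and within-period correlations is required". Because no evidence on their size is available, the authors "assume that the (within-centre) between-period correlations are zero" and power the trial as a cluster randomised design. "The intra-cluster (within-centre) correlation coefficient was set to be 0.01". The same section says of the crossover that "it is incorporated fully in the analysis of the primary study outcome".

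According to Randomisation and blinding (Table 2), each centre alternates between methods month by month. Every consenting woman at a given centre in a given month is therefore allocated the same method. Participants are to be "recruited from four English Breast Screening centres across different regions".

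**The concern.** The two methods are compared between centre-months. Variation from one centre-month to another, beyond a stable centre effect and a month effect shared by all centres, therefore enters the variance of the treatment effect directly. Such variation is plausible: staffing or local procedure at a centre may change from month to month, and the article itself names staff communication skills and centre processes as influences.

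The listed model has no term for it. If the variation exists, the confidence interval for the primary effect is too narrow and the test rejects a true null hypothesis more often than 5% of the time. The same would apply at 3 and 6 months. The line also sits badly with the sample size section, which distinguishes within-period from between-period correlation and then says that the analysis covers the crossover in full.

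**Working it through.** **1. The plan's own figure.** The design effect is 1 + (m − 1) × ICC. The article says "this led to the number of observations within a cluster to be 48.2" and "This gave a design effect of 1.49". With m = 48.2 and ICC = 0.01, 1 + 47.2 × 0.01 = 1.472, and 194 × 1.472 = 285.6, so 286. With the stated 1.49, 194 × 1.49 = 289.06, so 290 as stated. The figure reproduces closely enough, and I use 290. (The division described, 194/4/2, gives 24.25 and not 48.2. That is a separate matter and does not affect what follows.)

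**2. What the listed effects imply.** Let the centre variance be A and the variance of a period effect shared by all centres be B.

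| Pair of women | Covariance under the listed model |
|---|---|
| Same centre, same month | A + B |
| Same centre, different month | A |
| Different centre, same month | B |

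A between-period correlation of zero means A = 0. Two women in one centre-month are then no more alike than two women at different centres in that month. The ICC of 0.01 has no place in the model. It needs a third variance, C, specific to the centre-month.

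**3. Size of the error.** Inputs: 290 women, 4 centres, and 12 months (the sample size section plans one year) or 6 months (Table 2). Women per centre-month: m = 290/48 = 6.04 or 290/24 = 12.08. I assume equal cells, a two-sided 5% test, and all of the ICC specific to the centre-month.

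- Ratio of true to model variance: 1 + (m − 1) × ICC
- Ratio of standard errors: the square root of that
- True type I error: 2 × [1 − Φ(1.96 / ratio of standard errors)]

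| Months | ICC | Variance ratio | SE ratio | Type I error |
|---|---|---|---|---|
| 12 | 0.005 | 1.025 | 1.013 | 5.3% |
| 12 | 0.01 | 1.050 | 1.025 | 5.6% |
| 12 | 0.02 | 1.101 | 1.049 | 6.2% |
| 12 | 0.05 | 1.252 | 1.119 | 8.0% |
| 6 | 0.01 | 1.111 | 1.054 | 6.3% |
| 6 | 0.05 | 1.554 | 1.247 | 11.6% |

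Only 0.01 is the plan's value; the other ICCs are assumed to show the range.

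**4. In PCQ points.** The article states no SD. A difference of 3 points with 97 per arm and 80% power implies 3 × √(97/2) / (1.96 + 0.8416) = 7.46. Ignoring baseline adjustment, the model SE is 2 × 7.46/√290 = 0.876. The true SE at ICC 0.01 over 12 months is 0.876 × 1.025 = 0.898. The half-width of the 95% interval should be 1.76 points and would be reported as 1.72.

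**5. Simulation.** There were 100,000 trials per setting: 288 women in equal cells, centres split 2:2 between the arms, and no covariates.

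| Months | ICC | Rejection, term omitted | Rejection, term included |
|---|---|---|---|
| 12 | 0 | 5.2% | 4.0% |
| 12 | 0.01 | 5.7% | 4.3% |
| 6 | 0.01 | 6.4% | 4.1% |
| 12 | 0.05 | 8.2% | 4.7% |

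The Monte Carlo standard error is about √(0.057 × 0.943/100,000) = 0.07 percentage points. The simulation agrees with the formula.

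**The case against.** The strongest answer is that the line on random effects is ambiguous. It does not say whether period is crossed with centre or nested in it. The sample size section treats within-period and between-period correlation as the important quantities, so a period effect within centre may be what the authors meant, and that is the term at issue. A fuller analysis plan is promised and is not shown. This stands as a possibility and makes the point conditional. It does not remove it: the article introduces the list as the model set-up, and the nested reading is not written there.

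A second answer is that the zero between-period correlation was chosen as a conservative planning value, not as a belief about the data. The 0.01 is called a within-centre ICC, and the cluster size of 48.2 is close to a whole centre (194/4 = 48.5). This also stands. If only half of the 0.01 is specific to the centre-month, the type I error is 5.3%. Adjustment for baseline and covariates could absorb some of the variation as well.

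Three stronger readings are tempting and are not supported.

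- A reader might infer that women in the same centre-month are analysed as independent. They are not: a random centre effect correlates all women at a centre, and only the extra centre-month correlation is left out.
- A reader might take the design effect of 1.49 as the variance error. It rests on clusters of about 48, whereas a centre-month holds about 6 women over a year.
- A reader might conclude that a random centre effect with four centres is wrong. Each centre uses both methods, so centre effects largely cancel from the comparison, and fixed or random centre is a modelling choice.

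**Conclusion.** The point holds as a conditional one. On the plain reading, the stated primary model omits the correlation at the level at which the method is allocated, and it does not match the correlation structure behind the sample size. The direction of the error is anti-conservative.

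Its size at the plan's own ICC is small: the SE ratio is 1.025 and the type I error about 5.6% over the planned year, or 1.054 and 6.3% over six months. A reader might infer that the primary test is seriously invalid; at these parameters it is not. The larger errors, about 8% over 12 months and 11.6% over 6 months, require an ICC of 0.05, five times the planned value and wholly specific to the centre-month. They are relevant only because the article says nothing is known about these correlations, so 0.01 cannot be taken as an upper limit. The figures assume equal cells, 290 women at time point 2 and no absorption by covariates.

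**What to change.** State in the analysis plan that the primary model contains a random intercept for centre-by-period (centre-month) in addition to the centre and period effects, and name a small-sample degrees-of-freedom method such as Satterthwaite. If period was meant as nested in centre, say so in those words. Use the same model for the 3- and 6-month PCQ scores. Whether centre and month enter as fixed or random can be left to the statistician.

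The cost is one extra variance term and slightly wider intervals. In the simulation above, the test with the term was somewhat conservative, at about 4.1% to 4.3% for an ICC of 0.01. According to Current study status, no results go to the statisticians until recruitment closes, so at the time of the article the change could be made without sight of outcome data.

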**Methods and analysis:**

This is a multi-centre cluster randomised crossover trial in the English National Health Service Breast Screening Programme (NHSBSP) involving repeated survey measures at four time points. Participants will be women of screening age who have a biopsy following a suspicious mammography result, who ultimately receive a benign or normal (B1) result. Centres will trial both telephone and in-person results on a month-by-month basis, being randomised to which communication method will be trialled first. Women will be blinded to the method of communication they will receive. The analysis will compare women who have received telephone results and women who have received in-person results. The primary outcome measure will be anxiety (measured by the Psychological Consequences Questionnaire) after receiving results, while controlling for baseline anxiety. Secondary outcome measures will include anxiety at 3 and 6 months post-results, understanding of results and patient preferences for how results are communicated. Qualitative telephone interviews will also be conducted to further explore women’s reasons for communication preferences. Qualitative and quantitative data will be integrated after initial separate analysis using the pillar integration process.

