### Randomisation and blinding

Each centre will be randomised to one of two intervention arms by computer generated random numbers from the trial team base at the University of Warwick (see table 2). The arm relates to whether the first month at each centre will be telephone or in-person results. Each centre will commence with the communication method randomised in month 1 and continue to alternate between the two communication methods for the duration of the study. This approach allowed for each centre to use both methods of communication, controlling for previous experience (eg, centres who already telephone are more experienced and therefore women receiving telephone results from this centre might be less anxious).

**Table 2 T2:** Allocation of communication method by arm of the trial

Month	Arm 1	Arm 2
1	Telephone	In-person
2	In-person	Telephone
3	Telephone	In-person
4	In-person	Telephone
5	Telephone	In-person
6	In-person	Telephone

This approach was selected instead of a block approach, where each centre would deliver 6 months in-person followed by 6 months of telephone. The reason for this was to avoid potential bias from unforeseen centre drop out.

This design was chosen to ensure balance between trial arms at each site while addressing practical constraints. Balance between trial arms at each site is important to account for centre-level confounders such as staff communication skills and centre-level processes.

Individual randomisation was not possible as it interfered with screening centres workflow and fail-safe mechanisms to ensure that every woman was contacted with the correct information within the correct time frame.

Women will be allocated to receive their result based on the date of their attendance at the assessment visit. However, participants will be blinded to the randomisation month. Participants will only become aware of the communication method allocated when the results are received (see ‘Allocation of communication method’ section below for further detail). Breast screening staff will not be blinded, as they will be delivering the results and scheduling the appointments.

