### Allocation of communication method

There are two types of centres who may be involved in the research: centres who currently deliver benign results in-person and centres who currently deliver benign results by telephone.

For centres currently delivering results in-person, the following process for scheduling a results appointment will be observed: During in-person study months, all consenting women at time point 1 will be given an appointment to re-attend to receive their results in-person and will receive the result in-person. During telephone study months, all consenting women at time point 1 will be given an appointment to re-attend to receive their results in person. However, they will instead be telephoned prior to their scheduled appointment. Only benign women will be telephoned, with all women receiving other results (eg, cancer) attending their scheduled appointment.

For centres currently delivering results by telephone, the following process for scheduling a results appointment will be observed: All consenting women will be informed that, when their results are ready, they will be contacted by telephone to arrange an appointment to come back for their results. During the ‘telephone’ months of the study, women will be telephoned as expected. However, instead of arranging an appointment during this telephone call, results will be delivered. This means that, for women who go on to have a cancer result, they can be telephoned to arrange an appointment to attend in-person, as expected. This is in line with standard practice at these centres. During the in-person months, all consenting women will be informed that, when their results are ready, they will be telephoned to arrange an appointment to come back for their results. These women will be telephoned to arrange an appointment to come back in-person, and at that appointment they will receive their benign/normal result.

All women not enrolled in the study will receive their screening result based on the current standard practice at the attended centre.

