##### Secondary outcomes

Longitudinal anxiety scores at 3 and 6 months will be analysed in the same way as the primary anxiety outcome.

Differences in understanding score between communication methods groups will be assessed using a logistic regression model, adjusting for fixed effects.

Outcome variable—subjective understanding score (binary—yes or no), objective understanding score (binary—right or wrong).Fixed effects—age, ethnicity, previous attendance, previous biopsy, education, marital status.Comparator variable—method of communication received (telephone/in-person).

Preference data from the quantitative surveys will be presented in the form of percentages. All analyses will be implemented using IBM SPSS Statistics V.25.

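### The PCQ and understanding analyses compare women by the method of communication received, not the method allocated to their centre-month, so any anxiety-related departure from allocation would weaken the randomised comparison

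*Protocol article*

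**What the plan says.** Under Randomisation and blinding, the protocol article randomises centres to an order of alternating months: "Each centre will be randomised to one of two intervention arms by computer generated random numbers". A woman's own allocation then follows from a fixed date: "Women will be allocated to receive their result based on the date of their attendance at the assessment visit".

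The analysis sections sort women differently. Analysis, Primary outcome, gives "Comparator variable—method of communication received—telephone or in-person". Analysis, Secondary outcomes, names the same comparator for subjective and objective understanding, "Comparator variable—method of communication received (telephone/in-person", and carries the primary model over to time points 3 and 4: "Longitudinal anxiety scores at 3 and 6 months will be analysed in the same way as the primary anxiety outcome". The abstract agrees ("The analysis will compare women who have received telephone results and women who have received in-person results"), and the primary outcome definition contrasts "women who receive results in-person and women who receive results over the telephone".

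Study design credits randomisation with controlling confounding in the comparison of women who received each method. The article does not mention intention-to-treat or analysis as randomised, and does not say how to class a woman whose result came by the non-allocated method.

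**The concern.** Randomisation protects the groups defined by allocation. Groups defined by what happened afterwards have that protection only so far as the two coincide. Here allocation is known for every woman from her visit date, yet the stated comparator is a later event.

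The procedures leave room for the two to differ. At centres that normally give results in person, a woman in a telephone month still holds a clinic appointment; "However, they will instead be telephoned prior to their scheduled appointment". A woman who is not reached in time has an in-person route already booked. At centres that normally telephone, women in in-person months are rung to arrange a visit, so disclosure during that call is conceivable. Staff know the allocation, schedule the appointments and deliver the results.

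If being hard to reach, or pressing for an answer, goes with anxiety, the as-received groups would differ on the primary outcome for reasons unrelated to the method. Baseline PCQ, age, ethnicity, previous attendance, previous biopsy, education and marital status are all in the model, but they do not measure availability or requests for the result after the assessment visit. A partly confounded contrast could then be reported as a randomised effect.

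**Working it through.** **The plan's own figures.** No stated figure depends on the choice of comparator. From Sample size considerations: 194 × 1.49 = 289.06, rounded up to 290; and 194 / (0.85 × 0.50) = 456.5, rounded up to 457. Both reproduce, and neither changes if the comparator becomes the allocated method.

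**Inputs for the illustration.** The target difference is 3 PCQ points, with 97 women per arm before clustering, 5% significance and 80% power (Sample size considerations). The rest is assumed, because the article gives neither quantity:

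- p, the share of telephone-month women who get their result in person: 5%, 10% or 20%, with no switching the other way;
- d, how much higher the switchers' time point 2 PCQ is than other women's, after the model's adjustment: 4 points, with 2 and 7.45 as a range (7.45 is about one implied SD, derived below);
- telephone and in-person months of equal size.

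**False difference with no true effect.** Set the mean of non-switchers to 0.

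- Telephone received: only non-switchers, mean 0.
- In-person received: in-person-month women (size 1, mean pd, because randomisation puts the same share of would-be switchers there) plus switchers from telephone months (size p, mean d). The mean is (pd + pd)/(1 + p) = 2pd/(1 + p).
- In-person minus telephone, as received: 2pd/(1 + p). As allocated: pd − pd = 0.

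| p | d = 2 | d = 4 | d = 7.45 |
|---|---|---|---|
| 5% | 0.19 | 0.38 | 0.71 |
| 10% | 0.36 | 0.73 | 1.35 |
| 20% | 0.67 | 1.33 | 2.48 |

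At d = 4 these are 0.38/3 = 13%, 0.73/3 = 24% and 1.33/3 = 44% of the target.

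**Where it vanishes.** At p = 0 the two analyses are identical. Suppose instead that a further share p of women would switch from in-person to telephone, with the same d. Telephone received then has mean (pd + pd)/1 = 2pd, and so has in-person received. The difference is 0.

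**Price of analysing by allocation.** With a true 3-point effect and one-way switching, the expected estimate is 3(1 − p): 2.85, 2.70 and 2.40 at 5%, 10% and 20%. The article gives no SD. The one implied by 97 per arm, taking the test as two-sided, is 3 × √(97/2) / (1.960 + 0.842) = 7.46. Ignoring clustering, power then falls from 80% to about 76%, 71% and 61%.

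**The case against.** The strongest reply is that *received* may be loose wording. The article also uses the verb for the allocated condition ("Women will be allocated to receive their result based on the date of their attendance at the assessment visit"), never calls the analysis as-treated, and never says that a woman who departs from allocation is moved to the other group. It promises a fuller statistical analysis plan, where rules for non-adherence are usually set. This has some force on intent. It does not remove the point: the comparator is written into both formal model specifications and echoed in the abstract and the outcome definition. An analysis plan using allocation would have to contradict that text.

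A reader might go further and infer that the randomised comparison is lost, or that crossover is likely. The documents support neither. They report no departures and give no rate. Allocation of communication method does not say what happens to a woman who is not reached by telephone. For in-person months at telephone centres, it says that the call arranges the visit and the result is given at the visit. Women are blinded to the method until results arrive, and at telephone centres they are told the same thing in both kinds of month; this limits switching driven by preference. Both routes to crossover are therefore inferences.

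A reader might also take the 0.38 to 1.33 points as an estimate of bias. It is not one. A d of 4 exceeds the trial's own target difference, must be what remains after covariate adjustment, and has no support in the documents. Nor does its direction: nothing says that women who are hard to reach are more anxious.

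Finally, not every outcome is affected. Preferences are reported only as percentages, so the point covers PCQ at time points 2, 3 and 4 and the two understanding outcomes.

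**Conclusion.** The point stands in limited form. As written, the plan specifies an as-treated comparison for PCQ and understanding, although allocation is fixed by the centre-month of the assessment visit. To the extent that women get results by the other method for anxiety-related reasons, the comparison loses the protection that Study design relies on, and the planned adjustment need not restore it.

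The size is unknown. Under one-way switching with d = 4, the false difference is 0.38 points at 5% and 1.33 at 20%, against a 3-point target. It is nil with full adherence or symmetric switching. This should be fixed, because the text sets the wrong comparator and the remedy is simple. It does not show that the trial's randomisation has failed.

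**What to change.** In Analysis, Primary outcome and Secondary outcomes, define the comparator as the method allocated to the centre-month of the woman's assessment visit, regardless of the method used. Apply this to PCQ at time points 2, 3 and 4 and to both understanding outcomes, and align the abstract and the primary outcome definition. Record the method actually used and report it by allocated arm. Keep the comparison by method received as a labelled sensitivity analysis.

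The change to the comparator is wording only: the assessment date already gives every woman's allocation, and 194, 290 and 457 stand. Current study status says that the statisticians receive no results until recruitment closes, so the change can be made before outcomes are seen. The real cost is dilution in proportion to crossover. It is small at 5% but not at 20%, which is a further reason to report crossover alongside the result.
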